## Abstract

**Background:**

Chronic metatarsalgia (CM) causes significant pain and disability, affecting quality of life. Foot orthoses (FOs) including medially wedged designs with a metatarsal pad decrease excessive plantar pressure under the metatarsal heads, which is a suggested risk factor for developing CM. This FOs model may be effective in diminishing pain and improving function in these individuals. Thus, the objective of this trial will be to compare the effects of medially wedged FOs with a metatarsal pad and sham FOs on pain and foot function in individuals with CM.

**Methods/design:**

This participant- and assessor-blinded superiority randomized controlled trial (RCT) with two parallel groups will be conducted in Trois-Rivières, Canada. Sixty-four participants with CM will be recruited from the Université du Québec à Trois-Rivières outpatient podiatry clinic and via social media invitations. They will be randomized into intervention (customized FOs) or control (sham FOs) groups and will be evaluated at baseline and after 6 and 12 weeks. The primary outcome will be: (1) mean pain during walking for the most painful foot during the past week. The secondary outcomes will be: (1) Foot Function Index, (2) Global rating of change and (3) the 5-level EQ-5D.

**Discussion:**

Medially wedged FOs with a metatarsal pad are expected to provide a greater reduction in pain and improvement in foot function compared to sham FOs. This trial will help guide FOs prescription recommendations for managing foot pain in individuals with CM in the future.

**Trial registration:**

ClinicalTrials.gov NCT06962475

## 1. Background

Foot musculoskeletal disorders cause significant impairments and disabilities for those affected [1]. Among the various types of foot pain, chronic metatarsalgia (CM) is the most prevalent [2]. Metatarsalgia represents 88% of all causes of foot pain [3], with a prevalence of 13–36% in adults [4]. It is characterized by persistent pain to one or more metatarsophalangeal joints, resulting from harm (whether of mechanical origin or not) to the anatomical structures associated with the joint, including bone, cartilage, capsule and ligaments, tendons, bursae and subcutaneous tissue, and skin [3]. Chronic metatarsalgia significantly reduces the quality of life of those affected, physically, psychologically, and socially [5]. Different treatment modalities are used for CM, such as stretching exercises, footwear modifications, and foot orthoses (FOs) [6,7]. The first-line treatment is conservative, and surgery should be considered only when conservative treatment fails. Nevertheless, there is little high-level evidence (level I) to support the efficacy of conservative treatments for CM [8].

The reduction of the mechanical overload under the metatarsal heads during locomotion is a fundamental aspect of CM treatment [7], and it strongly correlates with pain reduction [9]. Foot orthoses are commonly used devices to reduce pain and improve function in individuals with musculoskeletal disorders [10–12]. They reduce forefoot plantar pressure during locomotion in individuals with CM and redistribute plantar pressure more evenly [13,14]. Metatarsal pads, a common FOs modification, effectively redistribute forefoot plantar pressure and thus reduce pain caused by excessive metatarsal loads [9,15–17]. Adding a medial wedge to FOs (inclination in the frontal plane) further reduces forefoot peak pressure in healthy adults [18]. While FOs tested so far are generally effective in managing CM, their effects can be inconsistent across patients, some patients did not find them effective [19–21]. From a biomechanical standpoint, FOs reduce mechanical overload; however, it is crucial to determine whether they also effectively reduce pain and improve foot function. Randomized controlled trials (RCT) are considered the gold standard for evaluating treatment effectiveness and efficiently translating research findings into clinical practice. This study design will allow us to assess whether, in addition to their biomechanical effects, FOs provide clinical benefits for individuals with CM.

The objective of this RCT will be to evaluate the effectiveness of medially wedged FOs with a metatarsal pad in reducing pain and improving foot function in individuals with CM. The hypotheses of this RCT will be that medially wedged FOs with a metatarsal pad will reduce pain and improve foot function compared to sham FOs.

## 2. Materials and methods

### 2.1 Study design

The study is a RCT with a parallel-group design, conducted as a participant- and assessor-blinded superiority trial. In this trial, participants with CM will be allocated to either the intervention group (customized FOs) or the control group (sham FOs) (Fig 1). All proposed methods are in accordance with the CONSORT statement which provides relevant guidelines and regulations for RCTs (S1 Checklist) [22]. The study protocol is reported using the Standard Protocol Items: Recommendations for Interventional Trials (SPIRIT) guidelines (Fig 1) (S2 Checklist) [23] and registered on ClinicalTrial.gov (Protocol ID: 2025_UQTR_FOs_RCT; NCT Number: NCT06962475).

**Fig 1 pone.0340905.g001:**
[figure not shown]
Study schedule of enrollment, interventions, and assessments according to SPIRIT 2013 requirements. (FOs: Foot orthoses; FPI: Foot Posture Index; FFI: Foot Function Index).

### 2.2 Recruitment

#### 2.2.1 Recruitment parameters.

Participants will be recruited from the *Université du Québec à Trois-Rivières* (UQTR) outpatient podiatry clinic and via social media invitations. The estimated start date for recruitment is early January 2026, and the estimated final date is early January 2027. Analysis of preliminary results will be conducted 6 months after the start of recruitment, if half of the participants have been recruited, or as soon as recruitment is completed. Results will be given no later than August 2027, if recruitment has been completed. We will obtain written consent once the participant has been included in the study (validation of inclusion and exclusion criteria and explanation of the protocol). They will be randomized to one of two groups, each receiving a different model of FOs (customized or sham). The total duration of participation will be 4–5 months (from the first contact until the last data collection). Participants will receive $25 after each follow-up (6 weeks and 12 weeks), for a total amount of $50. This financial compensation is intended to compensate participants for their time.

#### 2.2.2 Eligibility criteria.

Participants will be included if they [1] are aged 18 years or over, [2] have bilateral or unilateral metatarsalgia under one or more of the lesser metatarsal heads for at least 3 months (pain score of ≥ 4 out of 10 on a Visual Analogue Scale (VAS)) [24] that is aggravated by weight-bearing activities, [3] are able to walk without assistive devices (e.g., cane, walker), [4] are willing to wear shoes that will accommodate their FOs on a daily basis and [5] are willing to minimize the use of other interventions (e.g., pain medications, physical therapy) during the trial period. If they have bilateral CM, the most painful foot will be used for data collection. The pain score refers to the highest daily pain experienced over the week prior to their enrollment in the study. The CM diagnosis will be made by a podiatrist who, following the definitions of primary and secondary metatarsalgia and excluding other possible pathologies, will determine whether the patient have metatarsalgia (for example: primary: congenital deformities of the metatarsal heads; secondary: synovitis, predislocation syndrome) [7]. Potential participants will be excluded from the study if they have arthritis, neurological diseases (e.g., intermetatarsal neuroma) or other mechanical pain, plantar corns (e.g., intractable plantar keratoma), a history of orthopedic foot surgery, prior use of customized FOs, cognitive impairments, or if they are pregnant.

### 2.3 Interventions

A podiatrist with more than 11 years of clinical experience will take the negative foot impressions using a semi-weightbearing method with a foam box for both groups to ensure adequate blinding of participants and will have them sign the consent form. Then, the foam boxes of the experimental group will be scanned so that customized FOs can be 3D printed, and sham FOs moulded on a plaster replica of the foot. Both groups will receive identical clinical guideline-based information and support at the beginning of the trial. The instructions will be as follows: [1] undertake a familiarization protocol of 5 to 14 consecutive full days [25], [2] wear the FOs (customized or sham) at all time when they are standing (targeted minimum of 5 hours per day), [3] avoid positions that cause the metatarsophalangeal joints to dorsiflex (e.g., squatting or tiptoeing), [4] mechanical stress load management according to the tissue stress model [26], [5] not to walk barefoot and [6] wear shoes with good cushioning in which the FOs will be properly placed.

#### 2.3.1 Customized foot orthoses.

Participants randomized to the intervention group will receive customized FOs for both feet. The customized foot orthoses will be manufactured with a Nylon (PA11) shell with 6° medially wedged forefoot-rearfoot posts (2.6 mm if the participants’ weight (PW) is inferior or equal to 45 kg; 3.2 mm if 45 < PW ≤ 100 kg; 4.0 mm if PW > 100 kg), a full-length 3 mm Poron top cover, a metatarsal pad (15 shore A) located 5 mm proximal to the metatarsal heads [9], a 1.5 mm Multiform top cover on top of a 1 mm Black Leatherette layer (Fig 2).

**Fig 2 pone.0340905.g002:**

Customized foot orthoses (left: medial view, right: top view).

#### 2.3.2 Sham foot orthoses.

Participants randomized to the control group will receive sham FOs for both feet. The molded sham FOs will be manufactured from 3 mm ethylene vinyl acetate on top of a 1 mm Black Leatherette layer. They will have an identical top cover material, color and a similar shape than the customized FOs, however, they will provide negligible mechanical support, considering the very low stiffness of their medial arch. The only impact of these FOs on plantar pressure is under the heel [27]. These devices have been used as a sham condition in previous trials [28] and a study has validated them as being credible [27] (Fig 3).

**Fig 3 pone.0340905.g003:**

Sham foot orthoses (right: medial view, left: top view).

### 2.5 Data collection

Once the FOs are manufactured, participants will return to UQTR to collect them. During this visit, they will complete the initial questionnaires, and plantar pressure measurements will be taken with and without FOs. The plantar pressure will be collected with a Pedar-X in-shoe pressure measurement system (Novel Corporation, Munich, Germany), sampling at 100 Hz. The insoles of this system will be inserted between the foot and either the insole of the shoe or the FOs. Once they are equipped with the plantar pressure system, the participants will be allowed five minutes of acclimatization. Then, they will walk 10 times at a self-selected speed on a 10-meter walkway. The second and third assessments will be completed by phone or visioconference by a member of the research team, blinded to the group allocation of the participants. We will use MATLAB R2024b (The MathWorks Inc., Boston, MA, USA) for randomization and Qualtrics for the questionnaires.

### 2.6 Blinding and monitoring

Participants will be blinded as to which group they are allocated to and will not see the other participants. The researchers performing data collection as well as those performing statistical analyses will also be blinded to the group allocation. Participants will be advised that the trial has been designed to compare one of two types of orthopedic insoles for CM, but they will not be informed about the specific characteristics of the interventions. Given the nature of the intervention (i.e., FOs), it is not possible to blind the research staff responsible for their administration. To maintain consistency, the interventions will be described as “orthopedic insoles” throughout the study. If their FFI increases by 20% or more, then they will be prevented from continuing the study to avoid worsening the symptoms. The participants will complete a daily log of foot orthoses wear time and the use of various interventions (with text messages), if they do not wear their foot orthoses for a minimum of 3 hours per day on average, they will be excluded from the study. All adverse events will be recorded, assessed for severity and relatedness to the intervention, and reported to the Trial Sterring Committee.

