### 2.9 Sample size

To calculate pooled variance (σp²) and square of detectable difference (Δ²), we relied on pain data from a 3-month clinical trial with customized foot orthoses [6] and sham FOs [38].

**Pooled standard deviation:** σ_p_ ≈ 2.71 → σ_p_² ≈ 7.34**Detectable difference:** Δ = 1.49 → Δ² ≈ 2.22**Justification of Δ:** δ = 1.49 corresponds to the minimum clinically important difference on the VAS (≈15% of the scale), based on the study by Reina-Bueno, Vázquez-Bautista [38].α = 0.05β = 0.2**Sum of critical values squared:** (Z_1−α/2_ + Z_1−β_)² = (1.96 + 0.84)² ≈ 7.84

Considering the longitudinal design with three repeated measurements per participant (baseline, 6 weeks and 12 weeks), we estimated the effective variance per subject using a linear mixed-effects model with random intercept:

$${var}_{subj}=\;\sigma_{b}^{\text{2}}+\frac{\sigma_{w}^{\text{2}}}{m}\approx \text{1}.\text{4}\text{6}\text{8}+\;\frac{\text{5}.\text{8}\text{7}\text{2}}{\text{3}}\approx \text{3}.\text{4}\text{2}\text{5}$$

Using this variance, the sample size formula for two independent groups:

$$n\approx \frac{\text{2}\times ({\text{Z}}_{\text{1}-\alpha /\text{2}\;}+\;{\text{Z}}_{\text{1}-\beta })²\;\times {var}_{subj}}{\Delta^{\text{2}}}\approx \text{2}\text{5}$$

Therefore, the minimal sample size would be 25 per group. Considering an attrition rate of 20%, the final sample size should be 32 participants per group, resulting in a total sample size of 64 participants to detect significant differences for the primary outcome (VAS pain) at the primary timepoint (12 weeks). A sensitive analysis table showing required sample sizes under the different correlations (ρ = 0.3, 0.5, 0.7) is available in Supplementary Table S3 in S1 File.

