### 2.10 Statistical analyses

All analyses will follow the intention-to-treat principle, with additional per-protocol sensitivity analyses. Baseline characteristics will be summarized using means for continuous variables and frequencies (%) for categorical variables, without statistical testing between groups.

For the primary outcome (VAS pain), between-group differences will be analyzed using linear mixed-effects models, with participants included as random effects and baseline scores and minimization factors included as fixed covariates. The primary analysis will focus on the change from baseline to week 12, adjusted for baseline values, to provide a more precise estimate of the treatment effect. This approach allows all available baseline and follow-up data to be used, even in the presence of missing outcomes, under the assumption that data are missing at random. If the assumption of normally distributed residuals is violated, generalized linear mixed models will be considered as an alternative.

Secondary continuous outcomes (FFI – foot pain, FFI – disability, FFI – activity limitation, EQ-5D-5L index) will be analyzed using the same approach. The Global Rating of Change (GROC) will be modelled using ordinal logistic regression; a dichotomized responder analysis (effective vs ineffective) will be presented as exploratory. No formal multiplicity adjustments will be applied, but results will be interpreted with caution.

If missing data exceed 10% for the primary outcome, multiple imputation by chained equations will be used as a sensitivity approach, including all variables related to missingness and outcome prediction in the imputation model. Sensitivity analyses will also be performed under non-Missing At Random assumptions (e.g., using delta-adjustment or pattern-mixture models) to assess the robustness of the findings to departures from the Missing At Random assumption.

Concomitant care and rescue medication use will be recorded descriptively throughout the trial and summarized by treatment group. If substantial between-group differences are observed, these variables will be considered in sensitivity analyses.

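### Two post-randomisation rules in Section 2.6 end study participation rather than device use, so week-12 pain can go uncollected despite the intention-to-treat analysis in Section 2.10

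*Protocol article*

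**What the plan says.** Section 2.6 (Blinding and monitoring) sets two rules that act after randomisation.

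- **Worsening:** "If their FFI increases by 20% or more, then they will be prevented from continuing the study to avoid worsening the symptoms".
- **Wear time:** participants keep a daily log, and if "they do not wear their foot orthoses for a minimum of 3 hours per day on average, they will be excluded from the study".

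Section 2.10 (Statistical analyses) states: "All analyses will follow the intention-to-treat principle, with additional per-protocol sensitivity analyses". The primary model for VAS pain is a linear mixed model, "with participants included as random effects and baseline scores and minimization factors included as fixed covariates". On the contrast of interest: "The primary analysis will focus on the change from baseline to week 12, adjusted for baseline values". On missing outcomes: "This approach allows all available baseline and follow-up data to be used, even in the presence of missing outcomes", on a missing-at-random assumption. It adds: "If missing data exceed 10% for the primary outcome, multiple imputation by chained equations will be used as a sensitivity approach". Analyses that depart from missing at random are also planned.

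Section 2.9 (Sample size) allows for losses: "Considering an attrition rate of 20%, the final sample size should be 32 participants per group". Section 2.5 has the week-6 and week-12 assessments done by phone or video.

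**The concern.** Intention-to-treat needs the outcomes of everyone randomised, whether or not they kept to the intervention. Both rules in Section 2.6 are worded as leaving the study, and no section provides for assessment afterwards. Where a rule acts before week 12, the primary outcome is not collected.

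The resulting missingness would not be incidental. It would follow from low adherence or from worsening, and the customised and sham devices may differ in both, so removals may differ by arm. The primary model as described contains neither wear time nor FFI, the two variables that trigger removal. An analysis plan can define analysis sets and add imputation, but it cannot recover values that the conduct rules stopped collecting.

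The per-protocol sensitivity analysis is affected too. If it is to contrast adherent participants with everyone randomised, the low wearers must remain in the intention-to-treat data. Early removal takes them out of the observed week-12 values of both analyses.

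**Working it through.** **Step 1. What each rule loses, by timing.** The FFI is scheduled at baseline, 6 and 12 weeks (Abstract). Wear is logged daily (2.6), with no averaging window stated and no statement on whether the 5 to 14 familiarisation days (2.3) count.

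| Rule | When it acts | Follow-up pain values lost |
|---|---|---|
| Wear under 3 h/day | Before week 6 | Weeks 6 and 12 |
| Wear under 3 h/day | Between weeks 6 and 12 | Week 12 |
| Wear under 3 h/day | Averaged over all 12 weeks | None |
| FFI rise of 20% | Seen at week 6 | Week 12 |
| FFI rise of 20% | First seen at week 12 | None |

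A person removed before week 6 has no follow-up pain score, whether baseline enters as a covariate (2.10) or as one of three repeated measurements (2.9). The text does not say that data collected before removal leave the analysis, and that is not assumed here.

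**Step 2. Reproduce the planned sample size.** Inputs from 2.9: between-person variance 1.468, within-person variance 5.872, three measurements, difference 1.49, two-sided α 0.05, power 80%, attrition 20%.

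- Variance = 1.468 + 5.872/3 = 3.425.
- n per arm = 2 × 7.84 × 3.425 / 2.22 = 24.19, rounded up to 25.
- 25 / 0.8 = 31.25, rounded up to 32 per arm and 64 in total. This matches the protocol.

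With unrounded critical values, n = 2 × (1.96 + 0.8416)² × 3.425 / 1.49² = 24.22 per arm.

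**Step 3. Margin left after planned attrition.** 32 × 0.8 = 25.6 per arm remain. Power = Φ(1.49/√(2 × 3.425/25.6) − 1.96) = 0.821. If rule-based removals are additional, power reaches 80% at:

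- (25.6 − 24.22)/32 = 1.38/32 = 4.3% of those randomised, or 1.38 people per arm;
- 1 − 24.22/25.6 = 5.4%, if counted among those remaining after attrition.

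**Step 4. Power for assumed removal shares.** The protocol gives no input for how many people either rule would remove; 5%, 10% and 15% are assumptions.

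| Additional removals | n per arm (share of randomised) | Power | n per arm (share of those remaining) | Power |
|---|---|---|---|---|
| 5% | 24.0 | 0.796 | 24.32 | 0.802 |
| 10% | 22.4 | 0.769 | 23.04 | 0.780 |
| 15% | 20.8 | 0.738 | 21.76 | 0.757 |

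If removals lie within the 20%, power stays at 0.821. Section 2.9 does not say which applies.

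**Step 5. When imputation starts.** 10% of 64 is 6.4, so multiple imputation is used only from 7 missing values, and then as a sensitivity analysis.

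**The case against.** The strongest reply has four parts.

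1. **The wear rule may be harmless.** It speaks of an average and sets no interim check, so it may cover the whole 12 weeks and lose nothing. That reading is possible. But wear is logged daily and no window is stated, so the text also permits early removal. If the wording is meant to describe the per-protocol set, it still has to be changed, because it says study.

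2. **The FFI rule protects participants.** It does, and its safety purpose is stated. That justifies stopping the orthosis. It does not justify ending phone or video follow-up, which needs no device. On the schedule, only a rise seen at week 6 costs a value, and that person does have a week-6 pain score.

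3. **The planned analyses cope.** The mixed model uses the available data, imputation may include wear and FFI, and analyses outside missing at random are planned. These soften the problem and deserve credit. They still put assumptions in place of values that could have been collected.

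4. **The power loss is overstated.** Under the formula in 2.9, a person with two measurements has variance 1.468 + 5.872/2 = 4.404 and so keeps 3.425/4.404 = 78% of a full participant's information. The break-even for week-6 removals would then be 1.38/(32 × 0.222), about 19% of those randomised. This treats baseline and week 6 as near substitutes for week 12. The protocol's own variances imply a between-visit correlation of only 1.468/7.34 = 0.2, so the 78% does not describe the week-12 contrast. The point that stands is that Step 3 is also built on an averaged variance, so its figures are a gauge of the margin on the plan's own terms and not the exact power of the week-12 comparison.

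It is also fair that no bias has been demonstrated: low wearers could be people with little pain.

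**Conclusion.** The concern holds and should be fixed before participants are removed under these rules. Two stated conduct rules conflict with the stated intention-to-treat principle for the primary outcome, and values not collected cannot be recovered later. The conclusion rests on the wording and does not depend on the power figures.

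The cost in precision is conditional: none if removals fall within the planned 20% attrition; otherwise, from 82% to roughly 80%, 77% and 74% at assumed additional removals of 5%, 10% and 15% of those randomised. The sizes of any bias and of the removals themselves are unknown. The wear rule is the weaker of the two because no safety reason is given for it.

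**What to change.** Reword Section 2.6 so that neither rule ends follow-up.

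1. Keep the 20% FFI rise as a mandatory stop of the orthosis with clinical review, but not of outcome assessment. State whether 20% is relative or in scale points.
2. Delete the exclusion from the study for low wear. Use 3 h/day, with a stated averaging window, only to define the per-protocol set already planned in Section 2.10.
3. Continue the week-6 and week-12 phone or video assessments for everyone randomised and analyse them in the allocated arm. Keep the planned imputation and non-missing-at-random analyses for ordinary dropout.

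The cost is a change of wording, an ethics notification and a few extra calls by the existing route; the sample size stays at 64. The device safety stop is unchanged, which matters because Section 2.12 plans no independent data monitoring committee. The downside is that the intention-to-treat effect may be smaller, since it then includes low wearers and people who stopped the device.
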